## Introduction

The Dutch breast cancer screening programme, hereafter the programme, offers a biennial digital mammography (DM) examination to asymptomatic women aged 50 to 75. Craniocaudal (CC) and mediolateral-oblique (MLO) examinations are double-read by two screening radiologists independently and women with suspicious findings are referred to a hospital for diagnostic work-up [1].

In 2019, the detection and recall rates of the programme were 6.9 per 1000 women screened and 2.4%, which are among the highest and lowest, respectively, in Europe [2, 3]. Due to workforce issues, the screening interval has increased over the last years (towards 32 months), thereby increasing the detection rate to 7.9 per 1000 in 2022 at the same recall rate [4].

However, the 2D nature of DM results in well-known limitations [5]. Digital breast tomosynthesis (DBT) is an imaging technique that has been developed as a potential alternative to DM. Multiple studies have concluded that DBT improved screen-detected breast cancer rates, but that no effect has been seen on interval cancer (IC) rates [6, 7]. However, it should be noted that only two studies with DBT plus synthetic mammography (SM) reported IC rates [7]. Houssami et al also emphasised that their results were derived from studies on initial DBT examinations and that results on subsequent examinations may be different.

On average, DBT screening in European trials was found to increase the cancer detection rate to an average of 7.2 per 1000 for biennial screening [7]. Since the Dutch programme already nearly reaches this detection rate with biennial DM, it is unclear if DBT would increase detection. In addition, in Europe, recall rates for DBT screening decreased or increased, depending on the baseline DM recall rate [8]. Therefore, the already-low recall rate in the Netherlands could be expected to increase with DBT screening, but it is unknown to what extent. It is important to investigate the effects and acceptability of DBT in the Dutch screening setting to predict if DBT would be cost-effective [9, 10].

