## Data analysis

### Statistical analyses

The IC rate will be defined as the number of cancers, both in situ and invasive, diagnosed clinically (i.e., outside of screening) after a negative DBT in the first, second, and third year after the first screening round of the trial per 1000 screens (considering the longer screening interval). The AC rate will be defined as the number of tumours stage II or higher (TNM classification [17]) diagnosed after recall in the second screening round of the trial per 1000 screens. Data on screen-detected cancers (SDC) and IC, as well as their characteristics (e.g., stage and grade), will be obtained through linkage with the Netherlands Cancer Registry and the Dutch nationwide pathology databank for the intervention as well as the control group.

Secondary outcome measures including participation rate (i.e., percentage of participants in DBT or DM screening of the population invited), recall rate (i.e., number of women recalled for further examination per 1000 women screened), detection rate (i.e., number of women with SDC per 1000 women screened), and positive predictive value (i.e., percentage of women with SDC of women recalled) will be calculated for both screening rounds separately. The recall rate in the first round is expected to be higher due to the first-round effect of a more sensitive screening test, the learning effect for the radiologists, and the absence of prior DBT screens to compare to [18, 19]. The recall rate of the second round will estimate the long-term recall rate for DBT screening. The detection rate will be calculated for invasive and in situ cancers, overall and for cancer stage II or higher. Screening outcomes of both rounds will be stratified by breast density, as assessed by automated methods by Volpara (Mātakina Technology) and Quantra (Hologic).

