Screening outcomes for the two groups will be compared using the *χ*^2^ test to test differences between proportions and rates, overall and stratified by screening interval and breast density. The Fisher exact test will be used in stratified analysis with small groups. 95% confidence intervals will be calculated to consider the variability of proportions and rates. In addition, logistic regression analysis will be used to compare the results in the intervention and the control group by calculating the relative rates of the main screening detection measures, with 95% confidence intervals. The pain (scale 0–10), discomfort, and anxiety scores (4-point Likert scale) experienced in DBT screening will be compared to the experience of previous DM screening with paired *t*-tests and to scores on DM screening reported by a reference population with independent *t*-tests. A *p*-value ≤ 0.05 will be considered to indicate a statistically significant difference. Qualitative analyses in ATLAS.ti will investigate the answers to open questions on acceptability among participants, radiologists, and radiographers using inductive reasoning.

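### The plan uses logistic regression to produce relative rates, but that model gives odds ratios; the gap is negligible for rare outcomes and matters for PPV if PPV is included

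*Protocol article*

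**What the plan says.** The Statistical analyses section of the Protocol article sets out two layers of comparison between the arms.

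- **Tests and intervals.** "Screening outcomes for the two groups will be compared using the" chi-square test, with the Fisher exact test for small strata and 95% confidence intervals for proportions and rates.
- **Regression.** In addition, "logistic regression analysis will be used to compare the results in the intervention and the control group by calculating the relative rates". The same sentence gives the scope: "relative rates of the main screening detection measures, with 95% confidence intervals".

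The measures covered by that last phrase are not listed. The same section names participation, recall, detection and PPV as secondary outcomes, and defines PPV as a proportion of recalled women: "positive predictive value (i.e., percentage of women with SDC of women recalled) will be calculated for both screening rounds separately".

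**The concern.** The exponentiated coefficient of an ordinary logistic regression is an odds ratio. It is close to a ratio of proportions only when the outcome is uncommon in both arms. The sentence promises relative rates and mentions neither a log link nor standardisation, so the model and the effect measure do not match.

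An odds ratio always lies further from 1 than the corresponding ratio of proportions. If it is reported as a relative rate, both the estimate and its confidence limits exaggerate the change, in whichever direction it runs.

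The outcome to watch is PPV, which has recalled women as its denominator and is not rare. A change in PPV is plausible on the article's own account. The Introduction expects recall to rise from a low base and is unsure whether detection will rise with it. Statistical analyses expects higher recall in the first round. An inflated relative fall in PPV would make tomosynthesis look worse than it is in a trial meant to inform implementation.

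**Working it through.** **Inputs from the Protocol article**

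- Primary endpoint (Sample size calculations): 3.6 per 1000 with mammography and a reduction of 1.3, so 2.3 per 1000 with tomosynthesis.
- Programme figures for 2019 (Introduction): "the detection and recall rates of the programme were 6.9 per 1000 women screened and 2.4" per cent.
- Programme figures for 2022 (Introduction): "increasing the detection rate to 7.9 per 1000 in 2022 at the same recall rate".

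**The plan's own figure.** With 2.3 against 3.6 per 1000, two-sided alpha 0.05, power 80%, a 5:1 allocation, pooled variance and no continuity correction, the required intervention group is 17,275 and the control group 86,375. Both match the article. The planned rates are therefore read correctly, and nothing below alters the sample size.

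**Formulas.** Let p0 be the control proportion and p1 the intervention proportion.

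- RR = p1 / p0
- OR = [p1 / (1 − p1)] / [p0 / (1 − p0)]
- Overstatement of the relative change: (OR − 1) / (RR − 1) = 1 / (1 − p1)

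The last line shows that the overstatement depends only on how common the outcome is in the intervention arm. It is always above 1.

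**Rare outcomes.** The primary row uses the planned rates. The true RRs for detection and recall are assumed.

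| Outcome | p0 | p1 | RR | OR | 1/(1 − p1) |
|---|---|---|---|---|---|
| Primary endpoint | 0.0036 | 0.0023 | 0.639 | 0.638 | 1.002 |
| Detection | 0.0069 | 0.00897 | 1.30 | 1.303 | 1.009 |
| Recall | 0.024 | 0.036 | 1.50 | 1.519 | 1.037 |

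For recall with RR from 0.8 to 2.0, the overstatement runs from 1.02 to 1.05.

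**PPV.** The article gives no PPV, but its rates imply one:

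- 2019: 6.9 / 24 = 28.75%
- 2022: 7.9 / 24 = 32.9%

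The changes of 20% are assumptions. A fall of that size would follow, for example, if detection stayed at 6.9 per 1000 and recall rose from 24 to 30 per 1000: 6.9 / 30 = 23.0%, and 23.0 / 28.75 = 0.80.

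| p0 | p1 | RR | OR | Reads as | 1/(1 − p1) |
|---|---|---|---|---|---|
| 28.75% | 23.0% | 0.80 | 0.740 | 26% fall | 1.30 |
| 32.9% | 26.3% | 0.80 | 0.729 | 27% fall | 1.36 |
| 28.75% | 34.5% | 1.20 | 1.305 | 31% rise | 1.53 |
| 32.9% | 39.5% | 1.20 | 1.331 | 33% rise | 1.65 |

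First row in full: (0.23 / 0.77) / (0.2875 / 0.7125) = 0.2987 / 0.4035 = 0.740.

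Over assumed true RRs from 0.7 to 1.3, the factor runs from 1.25 (p0 = 28.75%, p1 = 20.1%) to 1.75 (p0 = 32.9%, p1 = 42.8%). The relative change in PPV is thus overstated by about 25% to 75%.

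**The case against.** The best defence is that the regression is confined to the main screening detection measures. For the outcomes that phrase most plainly covers, the odds ratio is a good stand-in for the rate ratio. That is correct, and it is why the point is minor. PPV is not named in the sentence. Including it is nevertheless a fair reading: its numerator is screen-detected cancers, it is listed beside recall and detection, and the sentence follows on from a comparison of all screening outcomes.

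Second, the regression is an addition. The proportions by arm, their intervals and the chi-square tests are planned separately and do not depend on how the regression output is labelled. An odds ratio of 1 is also a risk ratio of 1, so the null hypothesis is unaffected. This stands too: a reader could recompute the crude ratio from the reported percentages.

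Third, relative risks can be obtained from a logistic model by standardisation, and a full analysis plan that is not shown may do so. That is possible, but the published sentence pairs a model with a quantity that the model does not directly give, and should be corrected in any case.

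A reader might go further and infer a large distortion for participation, since odds ratios depart sharply from risk ratios when proportions are high. The document does not support this. Participation, defined as "participation rate (i.e., percentage of participants in DBT or DM screening of the population invited", is not plainly a detection measure, and no expected participation rate is given. The 95% under Sample size calculations is a re-attendance assumption applied to both arms, not a planned comparison.

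**Conclusion.** Wrong as written, and minor. The sentence names a model that yields odds ratios and calls the result relative rates, with no conversion stated. For the primary endpoint and the detection rate the difference is immaterial, and for recall it is small. For PPV, an odds ratio read as a relative rate would overstate the relative change by about 25% to 75%.

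The PPV result rests on three assumptions: that PPV is among the regression outcomes, that the control PPV is near the 28.75% to 32.9% implied by the 2019 and 2022 programme figures, and that the true RR lies between 0.7 and 1.3. The calculations are unadjusted. The documents do not support extending the point to participation or re-attendance, or suggesting that the primary conclusion is at risk.

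**What to change.** Revise the one sentence in Statistical analyses in two respects.

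1. List the outcomes that enter the regression, and say whether PPV is one of them.
2. Estimate risk ratios with 95% confidence intervals by log-binomial or modified Poisson regression, or by marginal standardisation of the logistic model. If the plain logistic model is kept, call its estimates odds ratios.

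The cost is a sentence or two and a change of model statement in the code. Unadjusted risk ratios need only counts and denominators by arm, so the aggregated control data described under Population and recruitment strategy are enough for them. No sample size, outcome definition or data collection changes.

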### Reading strategies

Multiple commercially available AI software solutions will be evaluated using all the data from the first round of the intervention arm. The software aims to detect malignancies in DBT images, highlight their location, and give a case-based and lesion-based score of probabilities of breast cancer. In agreement with the software vendors, the software description and the results will be reported anonymously. First, case-based probability of malignancy will be used to build recall rate/cancer detection rate curves and calculate the area under the receiver operating characteristics curve (AUC). All AI solutions with an AUC within 0.05 of the best-performing system will be used for the subsequent observer study.

With it or them, we will perform reader study sessions with ten screening radiologists to compare reading times with a dataset of 200 examinations. The dataset will be assembled from first-round cases and will include both cancer and negative cases (negative biopsies after recall and not-recalled cases verified by an expert panel). At the end of each session, the radiologists will complete a short questionnaire on the user-friendliness of each AI system. This subjective evaluation will be used in case the objective criteria of detection performance and reading time result in more than one computer system within the non-inferiority margin. The final chosen AI system will be the single one used in the evaluation of the interpretation strategies.

Four interpretation strategies for individual reading of the cases by a screening radiologist will be evaluated, combined with two different methods to achieve the double-reading of all cases, for a total of eight approaches for interpretation (Fig. 2), as follows:Standard: Acquisition of four views (CC and MLO) of DBT + the corresponding four SM images (Hologic). Interpretation using all images, with the DBT images displayed as stacks of slices with 1 mm separation.Single view DBT (MLO) + SM (MLO): Same as #1 but with interpretation of only the MLO views.Slabbed DBT + SM (CC + MLO for both): Same acquisition as #1 but with the DBT images displayed as 6 mm thick slabs with an overlap of 3 mm (3DQuorum Smart Slices, Hologic).AI-aided navigation: Same as #1 but interpretation performed with an accompanying computer system for navigation and decision support.

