**Fig. 2 Fig2:**
[figure not shown]
Flowchart of the eight reading strategies evaluated within STREAM. Every screening examination will be evaluated based on two radiologists and one radiologist and one AI prediction. The radiologists will evaluate every screening examination with four different strategies

The two double-reading strategies will include standard double-reading with a third reader in case of discrepancy between the first two readers, and AI as one reader and a radiologist as the second reader and another radiologist as arbiter in case of discrepancies.

Twenty radiologists will evaluate 200 examinations of the first round with each of the different reading strategies. The 200 examinations will be different from the examinations used for the first reader study, where we compare reading times and user-friendliness. Cases and reading strategies will be randomised in the usual manner, with the necessary four-week wash-out period between sessions. For each interpretation, we will record the location and probability of malignancy score for each suspicious lesion, and a recall/no recall decision, in addition to reading time. We will estimate the JAFROC figure of merit [20], and the case-based AUC for each of the DBT reading strategies studied.

To compare the result of using the standard double-reading by two screening radiologists to that of using hybrid AI-human double-reading, the results of the radiologists reading mentioned above and of the computer system analysis of these 200 cases will be used. For this, first, all interpretations by one radiologist will be paired at random with those of another, to replicate blinded double-reading by two independent radiologists. The AI-based results will be dichotomised into recall/no recall using the operating point that would result in the same average recall rate as the screening radiologists in the first screening round of this trial. Sensitivity and specificity of the final screening outcomes will be the endpoint of these studies.

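### AI systems within 0.05 of the best full-range AUC count as equal on detection, but the chosen one reads at a single low recall rate, where sensitivity can differ materially

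*Protocol article*

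**What the plan says.** All of this is in the protocol article, section Reading strategies, including the text after Fig. 2.

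- **Measures built.** On all first-round intervention data, "case-based probability of malignancy will be used to build recall rate/cancer detection rate curves", and the area under the ROC curve is calculated.
- **Entry rule.** "All AI solutions with an AUC within 0.05 of the best-performing system will be used for the subsequent observer study". That study has ten radiologists read 200 examinations to compare reading times.
- **Final choice.** "This subjective evaluation will be used in case the objective criteria of detection performance and reading time result in more than one computer system" still inside a margin; the full phrase is "more than one computer system within the non-inferiority margin". The only margin stated in the section is the 0.05 in AUC.
- **Consequence.** "The final chosen AI system will be the single one used in the evaluation of the interpretation strategies".
- **Use as a reader.** For hybrid double reading, the AI output is cut at "the operating point that would result in the same average recall rate as the screening radiologists in the first screening round". Sensitivity and specificity of the final screening outcome are the endpoints.

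The Introduction gives a programme recall rate of 2.4% with digital mammography. Statistical analyses expects first-round DBT recall to be higher but gives no value.

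**The concern.** Full-range AUC averages sensitivity over every false-positive rate from 0 to 1. The AI reader works at one point near the far left of that range. Two systems can be close in AUC and well apart at that point. Under the rule as written, the weaker of the two could be preferred because it reads faster or is better liked.

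The choice carries weight because a single system goes forward. It supplies the AI reader in all four hybrid double-reading approaches. If a strategy with AI is judged best, it also enters the second-round re-reading and the microsimulation inputs. The Discussion says the reading-strategy analysis cannot be redone within the funding period, so a poor choice could not be corrected there.

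**Working it through.** The article gives no derivation for the 0.05, so there is no figure of its own to reproduce. The check is what 0.05 in AUC means at the planned operating point.

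**Inputs from the article.** AUC margin 0.05; recall 2.4% (2019 programme); detection 6.9 per 1000 (2019) or 7.9 per 1000 (2022); 18,200 first-round DBT examinations.

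**Assumptions not in the article.** Binormal ROC with slope b from 0.6 to 1.0; best AUC from 0.85 to 0.97; total recall from 2.4% to 5%; cancer prevalence set equal to the programme detection rate.

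**Formulas.** AUC = Φ(a/√(1+b²)), so a = √(1+b²) × Φ⁻¹(AUC). With threshold t, false-positive rate = 1 − Φ(t) and sensitivity = Φ(a − b·t). The threshold t solves: prevalence × sensitivity + (1 − prevalence) × false-positive rate = recall.

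**Worked pair, b = 1, recall 2.4%, prevalence 0.0069**
- AUC 0.95: a = 1.414 × 1.645 = 2.326; t = 2.055; sensitivity = Φ(0.271) = 60.7%. Check: 0.0069 × 0.607 + 0.9931 × 0.0199 = 0.024.
- AUC 0.90: a = 1.414 × 1.282 = 1.812; t = 2.028; sensitivity = Φ(−0.216) = 41.5%. Check: 0.0069 × 0.415 + 0.9931 × 0.0213 = 0.024.
- Gap: 19.2 points. Expected cancers: 18,200 × 0.0069 = 126, so the gap is 0.192 × 126, about 24 cancers, for the AI alone.

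**How the gap moves with the assumptions**

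| Best AUC vs 0.05 lower | b = 1, 2.4% recall | b = 1, 5% recall | b = 0.6, 2.4% recall | b = 0.6, 5% recall |
|---|---|---|---|---|
| 0.97 vs 0.92 | 24.2 | 21.3 | 17.1 | 14.6 |
| 0.95 vs 0.90 | 19.2 | 18.4 | 14.6 | 13.1 |
| 0.90 vs 0.85 | 12.2 | 13.4 | 10.9 | 10.6 |
| 0.85 vs 0.80 | 8.4 | 10.1 | 8.7 | 8.9 |

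The range is about 8 to 24 points. A prevalence of 7.9 per 1000 changes the worked gap only to 19.1.

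**Equal AUC, different slope, 2.4% recall.** At AUC 0.95, b = 1 gives 60.7% and b = 0.6 gives 74.9%. At AUC 0.90 the figures are 41.5% and 60.3%. The AUC rule sees no difference in either case.

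**Precision available.** Cancers: 126, or 18,200 × 0.0079 = 144. For two sensitivities p and q measured on the same n cancers, SE = √{[p(1−p) + q(1−q) − 2r√(p(1−p)q(1−q))]/n}. With p = 0.607, q = 0.415 and an assumed correlation r of detection between systems of 0.3 to 0.5, SE is 5.2 to 4.4 points at n = 126 and 4.8 to 4.1 at n = 144: about 4 to 5 points.
- The half-width of a 95% interval is then 1.96 × 4 = 7.8 to 1.96 × 5 = 9.8 points, so it cannot fit inside a 5-point margin.
- In simulations of identical systems (126 cancers, 2.4% recall), observed sensitivities differed by more than 5 points in about 19 to 31% of runs.
- A rule that drops a system only when its paired 95% interval shows it to be worse flagged a true 16-point gap in 90 to 96% of runs. It wrongly dropped an equal system in about 2 to 3%.
- Smaller gaps are caught less often. By normal approximation, a 12.2-point gap is flagged with probability Φ(12.2/5 − 1.96) = 68% to Φ(12.2/4 − 1.96) = 86%.

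**The case against.** **The 0.05 rule is an entry screen, not the final selection.** Detection performance is listed again among the objective criteria before user-friendliness counts. That the later non-inferiority margin is the same 0.05 in AUC is a reading of the text, not something it says, and the full protocol may say more. This stands in part. But the article does fix a measure and a margin, gives no other, and attaches no criterion to the operating point.

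**AUC is a reasonable measure here.** It is the trial's stated outcome for comparing reading methods, it is estimated more precisely than sensitivity at one point, and the AI also serves navigation, which has no fixed recall threshold. This stands. A reader might infer that full AUC is simply the wrong measure and should be replaced. The documents do not support that; AUC is sound as an entry screen.

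**The size rests on assumptions.** A reader might take 20 points as the general cost of the margin. It needs a best AUC near 0.95, nearly equal variances and a competitor at the edge of the margin.

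**The harm to the trial is not shown.** A reader might infer that the trial would wrongly find AI-human reading inferior or not cost-effective. The figures are for the AI alone. In every hybrid approach a radiologist is the other reader and another radiologist arbitrates discrepancies, so an AI miss need not be a final miss. No loss in final sensitivity has been calculated.

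**The reference standard is incomplete.** The Discussion notes that interval cancers are unknown at this stage. A cancer that the AI flags and the radiologists missed would count as a false positive, probably near the working threshold. This limits any comparison there, and the remedy should allow for it.

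**Conclusion.** The concern holds in limited form. The article treats systems as equivalent on detection when full-range AUC is within 0.05 of the best. It can then choose on reading time and user-friendliness, while the chosen AI is used as a reader at one recall-matched threshold. Under a binormal ROC with slope 0.6 to 1.0, best AUC 0.85 to 0.97 and total recall 2.4% to 5%, systems at the two ends of the margin differ by roughly 8 to 24 points of stand-alone sensitivity. Differing ROC slopes can hide a gap even at equal AUC.

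This does not extend to AI-aided navigation or to the primary endpoint. The loss in final double-reading sensitivity is probably smaller and is not quantified here. The point is still worth acting on, because one system is carried forward, the strategy analysis cannot be repeated in the funding period, and the curves needed are already planned.

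**What to change.** Keep the AUC rule as the entry screen. Add one step before reading time and user-friendliness decide: compare the remaining systems on sensitivity, or on partial AUC around it, at the radiologists' first-round recall rate, read from the recall/detection curves already planned. Do not choose a system whose paired 95% confidence interval shows it to be worse there than the best. State that this step is the detection-performance criterion for the AI in its role as a reader, and say whether the non-inferiority margin named in the text is the 0.05 in AUC.

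Do not require the confidence interval to lie inside a 5-point margin. About 126 to 144 cancers cannot support it, and equally good systems would fail.

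Cost: a little extra analysis on scores already collected. Precision is limited (standard error of the paired difference about 4 to 5 points), so the step reliably excludes only large deficits. It also inherits a reference standard without interval cancers; the re-evaluation of the AI solutions planned after round 2 could repeat the same comparison.
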